### Analysis

#### Qualitative

All the interviews which had been recorded verbatim were transcribed and organised using the software NVivo (version 8.3). Demographic data from Baseline surveys were converted from Access to Unicode Text (*.txt) and imported into NVivo as a casebook. The responses to the open ended questions in the Teacher Exit Survey were exported from the Access database, converted to Word Documents, imported into NVivo and coded using the Auto Code function. This process ensured that an integration of the data sets could be achieved
[27]. We generated categories and sub-categories from the segments of the data, usually sentences and paragraphs; constantly checking the emergent understandings and clarifying these with the research team
[28]. The responses to the open-ended questions in the carer exit survey will be analysed in the same manner.

#### Quantitative

Percentages of detection of health screenings and health promotion activities initiated, and responses to postal questionnaires will be compared between the intervention and the usual care group using data extracted from medical records. The individual will be the unit of analysis. For continuous outcome variables, a mixed-effects linear regression model will be used to compare the outcomes between comparison groups, with allowance made for cluster and matching effects. For categorical outcomes, a mixed-effects logistic regression model will be used. Sub-group analysis of adolescents at particular risk, such as those with Down syndrome will also be performed.

The primary analyses will be based on the ‘intention-to-treat’ (ITT) principle; all individuals with evaluable data for the outcome under investigation will be analyzed in the group they were randomized to, regardless of treatment received. Additionally, ‘per protocol’ (PP) analyses will be conducted where there have been large deviations from the planned intervention; all individuals with evaluable data for the outcome under investigation will be analyzed according to the treatment received. Any such analyses will be clearly labeled as such and cautiously interpreted as perhaps indicating the maximum theoretical potential of these programs. The PP analyses will consist of three comparison groups according to the timing of the treatment received. The three groups are ‘intervention early’, ‘intervention late’, and ‘no intervention’. The ‘intervention early’ group will consist of individuals whose teachers reported they received their *Ask Health Diary* at the time they were scheduled to, or within 3 months of the time they were scheduled to, and parents/carers confirmed this had been received. The ‘intervention late’ group will consist of individuals who teachers reported they received their *Ask Health Diary* at least three months later than they were scheduled to and those who, when their parents/carers were contacted in July 2008, reported they had not received a diary. The ‘usual care’ group will consist of individuals randomized not to receive an intervention. The separate effects of the CHAP health check, the *Ask Health Diary* and the *Ask Project Curriculum Strategy Booklet* will be explored by comparing outcomes for individuals according to the number, and timing, of components of the health intervention package they received.

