### Randomisation

Allocation in this study was by cluster randomisation. The unit of randomisation was the school. Individual randomisation was inappropriate for this study as the teaching had to be done in the open classroom, even if lessons were individualised for each student. Consequently it was essential all students in a particular school were allocated to receive the same treatment (either the intervention or usual care).

Randomisation occurred after schools were stratified by type (Special Education Schools/Special Education Units/High Support Needs Schools) and location (Major City/Inner Regional/Outer Regional). Location was categorised according to the Accessibility/Remoteness Index of Australia classification
[23]. Within each stratum, schools were ranked according to the expected number of participating adolescents. Using the ranked list within each stratum, schools were formed into pairs. A list of computer-generated random numbers was used to allocate either the intervention or usual care treatment to the first of each pair; the second in each pair was allocated the alternative treatment.

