## Results

### Recruitment

Data were provided by Education Queensland as to the number of students in the 160 SESs and SEUs that met the inclusion criteria. Of the 160 schools, 59 were excluded as 49 had enrolments of less than 10, one had participated in the pilot project, six had student populations that were transient in nature and three schools were considered too remote. The recruitment officer contacted all eligible schools and offered to do a presentation for teachers. Of the 101 schools approached, 16 schools declined. Of these 10 considered it too difficult to incorporate the project into what was often an already over-crowed curriculum, two special education units thought it too simple for their students and four gave no reason (See Figure
2a).

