### Intervention

The program was scheduled to be taught in schools in the first term of 2007, but changes in the way teachers were allocated to schools at the beginning of that year meant that in first term there were major staff changes and, as a result, after randomisation but before we had sent out baseline surveys, we saw nine schools withdraw from the study. All schools reported difficulty in obtaining student consent, but more usual care schools than intervention schools withdrew from the study (See Figures
2a and
2b). New teachers in special education units randomised to the intervention group considered it appropriate to teach the program to incoming Grade 8 students which resulted in the inclusion of 12 year old adolescents in the study. Because of the organisational structure of special schools, some even younger students were also included which led to the revision of our age eligibility criteria to 10–18.

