### Data collection

#### Baseline surveys

The staff changes after randomisation resulted in 185 educators from the 41 intervention schools and 167 from the 35 usual care schools participating at baseline (See Figure
2a). At baseline there were a total of 728 adolescent participants in the study, 425 in the intervention group and 303 receiving usual care (See Figure
2b). After intensive follow-up we achieved a response rate of 64.5% (n = 352) for educator and 81.5% (n = 728) for carer surveys. Information was obtained directly from schools on intellectual functioning for 203 of the adolescents.

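### The stated model allows for clusters and matching but does not name the school-type and location strata, which leaves the 6 to 18 of 76 baseline schools without a partner unadjusted for them

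*Protocol article*

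**What the plan says.** The Randomisation section of the protocol article sets up a layered design. "Randomisation occurred after schools were stratified by type" (three levels) and by location (three levels), which gives at most nine strata. Within each stratum, schools were ranked by expected number of participants and paired. One school of the pair was allocated at random, and "the second in each pair was allocated the alternative treatment". No rule is given for a school left over in a stratum with an odd count.

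The Analysis section (Quantitative) makes the individual the unit of analysis. It uses a mixed-effects linear model for continuous outcomes, "with allowance made for cluster and matching effects". The next sentence reads "For categorical outcomes, a mixed-effects logistic regression model will be used". Type and location are not mentioned in the analysis.

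The Results section supplies the school counts. Under Recruitment: "Of the 101 schools approached, 16 schools declined". Under Intervention, after randomisation and before the baseline surveys, "we saw nine schools withdraw from the study", with more usual care than intervention schools leaving. Under Baseline surveys: "185 educators from the 41 intervention schools and 167 from the 35 usual care schools".

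**The concern.** A pair effect stands in for the strata only while both schools of the pair are analysed. Where one school is missing, the other has a pair effect to itself. If pair effects are random, that school joins the between-pair part of the treatment comparison with nothing to adjust it for type or location. If they are fixed, its own effect absorbs it completely and it contributes nothing to the treatment estimate, which sits badly with the intention-to-treat commitment to analyse everyone with evaluable data.

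Type could plausibly matter. The Participants section describes special-school students as having significant or multiple disabilities and unit students as usually following the mainstream curriculum, so health needs and GP activity may differ between them. Loss of schools was unequal by arm. If loss was also related to type, the unpaired schools would tilt the comparison.

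**Working it through.** **The plan's own figure first.** Design effect = 1 + (20 − 1) × 0.03 = 1.57, as stated. Effective size per arm = 500 / 1.57 = 318.5. For 10% versus 19% at two-sided 5% (sidedness assumed):

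- Null standard error = √(2 × 0.145 × 0.855 / 318.5) = 0.0279.
- Alternative standard error = √((0.10 × 0.90 + 0.19 × 0.81) / 318.5) = 0.0277.
- z = (0.09 − 1.96 × 0.0279) / 0.0277 = 1.28, so power is 89.9%.

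The stated 90% reproduces. It takes no credit for matching or strata, so nothing below alters it.

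**Schools randomised.** 101 − 16 = 85, and 41 + 35 + 9 = 85. The article does not print this total, but two routes agree. It is odd, so at least one school had no partner. With up to nine strata, each possibly odd, the number could be 1, 3, 5, 7 or 9.

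**Schools without a partner at baseline.**

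- Lower bound: intact pairs cannot exceed the smaller arm, 35. Unpaired = 76 − 2 × 35 = 6. This is attainable with one single at allocation, two pairs lost whole and five half-lost: 5 + 1 = 6.
- Upper bound: nine singles at allocation leave (85 − 9) / 2 = 38 pairs. If the nine withdrawals fall in nine different pairs, 29 stay intact. Unpaired = 76 − 2 × 29 = 18.
- With one single only, the range is 6 to 10.

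So 6 to 18 of 76 schools (8% to 24%) are unpaired, and 58 to 70 are in intact pairs.

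**Possible bias.** The documents give no outcome rates or withdrawals by school type, so these inputs are assumed:

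- 42 pairs plus one single, with 7 usual care and 2 intervention withdrawals (one split consistent with 41 and 35).
- 10 students per school (728 / 76 = 9.6), base rate 10% and ICC 0.03, with between-school variance split equally between pair and school.
- True treatment effect zero, and special schools 10 points above units in outcome rate.
- Units making up 30%, 50% or 70% of pairs.

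The treatment effect was estimated by generalised least squares on school means, with a random pair effect, with and without a type term. The range within a cell depends on whether the fitted pair variance also picks up the variation due to type.

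| Withdrawals | Share of units | Bias, pair only (points) | Bias, type added |
|---|---|---|---|
| All from units | 30% | −0.77 to −0.91 | 0.00 |
| All from units | 50% | −0.55 to −0.67 | 0.00 |
| All from units | 70% | −0.35 to −0.42 | 0.00 |
| Unrelated to type | 30% to 70% | within ±0.02 | 0.00 |

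A hand check at 50% units, ignoring pairs: 21 unit pairs leave 19 intervention and 14 usual care units. If the single is a special school, the shares of units are 19/41 = 46.3% and 14/35 = 40.0%, a gap of 6.3 points. Multiplied by the 10-point type difference, that is 0.63 points. If the single is a unit, 20/41 = 48.8% and the figure is 0.88. The pair term trims the average of these two.

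As a sensitivity, a 20-point type difference with all withdrawals from units gives −0.5 to −1.1 points when the pair variance absorbs type, and −0.8 to −1.8 when it is held at the ICC-based value.

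**Precision.** The standard error is about 2.3 to 2.4 points under both models. Adding type changes it by under 1% at a 10-point type difference and by about 2% at 20 points.

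**The case against.** The strongest reply is that a journal article condenses the analysis. It gives the models two sentences, and covariate lists and the handling of broken pairs usually go to a fuller plan that is not shown. Since pairs were formed within strata, allowance for matching already carries type and location for most schools, and the phrase could even be read as adjustment for the matching factors themselves.

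Much of this stands. The article does not exclude the strata, and intact pairs need no rescue. What remains is that the article chose to state its design adjustments, left the strata out of that statement, and itself reports the withdrawals that broke the matching. Adding the two factors improves on the model as stated.

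Three stronger readings are tempting and not supported:

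- A reader might infer that the treatment comparison is confounded with school type and location. No section gives withdrawals by type. The article links them to system-wide staff changes, and the two units that found the project too simple declined before randomisation.
- A reader might infer that the categorical model makes no allowance for design. That sentence directly follows the one naming cluster and matching and most naturally shares its terms.
- A reader might infer lost power or a materially wider interval. The precision effect is about 2% at most, and the power calculation never relied on strata.

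**Conclusion.** The point holds in a limited form. The stated model does not name the stratifying factors, and the matching term cannot supply them for the 6 to 18 of 76 baseline schools without a partner. Those bounds rest on the derived total of 85 and on pairing strictly within strata. They describe schools at baseline: GP records were obtained for 436 of 728 adolescents, and the number of schools behind those records is not given.

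For an assumed 10-point type difference with every withdrawal from units, the bias is about 0.3 to 0.9 points. That is roughly 4% to 10% of the planned 9-point effect and no more than about 0.4 of a standard error (0.91 / 2.32). If withdrawal was unrelated to type, it is near zero. The case for change rests on inexpensive protection against bias and on settling how unpaired schools are handled. It does not rest on an error in any stated figure.

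**What to change.** In the Analysis section (Quantitative), state that the primary linear and logistic mixed models include school type (three levels) and location (three levels) as fixed main effects, alongside random school and pair effects. State also that schools without a partner stay in the analysis, adjusted through these terms.

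The cost is one or two sentences and 2 + 2 = 4 degrees of freedom against 76 schools. Both factors were needed to randomise, so they are known for every school. Main effects are enough, because some of the nine type-by-location cells may be sparse. The sample size and power statements need no change.

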#### Exit surveys

Seventy-four (57.4%) of the 129 teacher exit surveys mailed were returned for analysis (See Figure
2a). Only 26 teachers reported that they began teaching the project in Term 1; 34 did not do so until Term 2; and others began even later in the year. Teachers also differed in the number of hours per week and the number of weeks taught. 47 teachers taught for one semester only, 23 taught over 2 semesters and 4 taught over 3 semesters. On average teachers taught for 11 weeks (SD = 7) and for 57 minutes per week (SD = 28).

Most diaries were not sent home from schools until June/July 2007, but others were not sent until third or in at least two cases fourth term. CHAP booklets were sent to carers of the intervention participants after all schools reported that the diaries had been sent home so that they might take their child to their doctor for the health check in November 2007. These delays required a revision of the original project timeline (Figure
1). Figure
3 shows the actual timeline.

Between Baseline and the Exit many participants were lost to follow up and 41 had no consenting GP so could not continue in the study. Of the 347 adolescents from the intervention group who completed the baseline survey, only 176 returned their CHAP booklets. Of the 486 carer exit surveys sent out in July 2009, 388 (79.8%) were returned (See Figure
4).

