##### Health outcome data

GP records were collected for 436 of the participants (See Figure
5). Depending on the time of collection and whether or not all GPs the adolescent had attended during the period had consented to participate in the study, data is available for each participant for a period up to 54 months between January 2006 and June 2010. Data was obtained for 195 of the usual care group, 161 of the intervention group who had completed both the educational and medical components of the intervention and 80 who had the educational intervention only, i.e. they did not do the CHAP.

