## Discussion

We describe the methodology employed that enabled us to perform a pilot and randomised controlled trial involving a hard-to-reach population in a complex naturalistic setting. Although we were required to modify the original protocol due to the nature of this population and the research environment, we maintained the integrity of the study. While our aim was to recruit 1000 participants, the sample size of 728 was still large and good response rates were obtained from both carers and GPs.

Our research strategy was based on our experience of trials in this population and the known barriers to conducting research in adults with intellectual disability. We used materials developed or informed by the previous randomised controlled trials in adults, such as CHAP booklets that have been demonstrated to be acceptable to people with intellectual disability and their families. We believe our success was also based on our awareness that decision-making in government departments and schools can be a political process
[29]. Our approach involved active communication and the development of relationships with all levels of the education system. We met with several tiers of governance in the Queensland Education Department to inform them and gain their support before accessing the schools and teachers. To maximise their understanding of the project, we provided direct contact and accessible written information. At all levels we attempted to convince staff that this project should be included in an already overcrowded curriculum. Prevention programs inevitably place extra burdens on school and student respondents
[30], so in order to encourage participation, schools were reimbursed for staff time. We persisted with reminders and consistent follow-up with school principals, senior, and classroom based, teaching staff. This approach appears to have diminished the known barriers and increased our ability to implement the research protocol.

There were also approaches we took which did not work as well as anticipated. We found a successful pilot project did not provide sufficient breadth of understanding of the usual situation in the school system to adequately inform the larger project. The principal in our pilot special school was enthusiastic, energetic and organised, characteristics found to aid implementation of school-based prevention programs

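### The primary analysis labelled intention-to-treat is available-case, and in the intervention arm having a GP record is strongly associated with CHAP uptake: a risk of bias whose size the article cannot settle

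*Protocol article*

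**What the plan says.** The Quantitative part of the Analysis section bases the primary analyses on the intention-to-treat principle and defines the set as "all individuals with evaluable data for the outcome under investigation will be analyzed in the group they were randomized to, regardless of treatment received". The models allow for cluster and matching effects. A per-protocol analysis is planned where delivery departed widely from plan, to be read with caution as a possible upper limit of what the programme can do. Comparisons by components received are also planned.

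The Results give the counts. At baseline there were "728 adolescent participants in the study, 425 in the intervention group and 303 receiving usual care". Under Exit surveys, of 347 intervention adolescents with a completed baseline survey, "only 176 returned their CHAP booklets"; 388 of 486 carer exit surveys sent were returned (79.8%). Under Health outcome data, "GP records were collected for 436 of the participants". "Data was obtained for 195 of the usual care group", and the intervention arm contributed "161 of the intervention group who had completed both the educational and medical components of the intervention and 80 who had the educational intervention" without the CHAP. The Discussion concludes that "good response rates were obtained from both carers and GPs".

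**The concern.** Analysing people in the arm to which they were randomised protects the comparison only if the people analysed still represent those randomised. Here two in five have no GP record, and in the intervention arm those with a record are disproportionately those who did the CHAP. The CHAP is the component in which the GP reviews the history, examines the adolescent and records findings. The sample size section names detection of vision or hearing impairment as one of the primary outcomes, and such outcomes are read from GP records. The filter is thus tied to the component closest to the outcome.

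At stake is what the main result means. If CHAP users gain more than non-users, a set that is two-thirds CHAP users moves from the effect of offering the package to everyone towards the effect in families who took it up, while carrying the intention-to-treat label. A model with only cluster and matching effects does not correct for this.

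**Working it through.** **Inputs.** Baseline 425 and 303 (Results, Baseline surveys). Booklets returned 176, among 347 survey completers (Results, Exit surveys). Records 195, 161 and 80 (Results, Health outcome data). Rates of 10% and 19% (Sample size).

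**The article's own figures reproduce.** 425 + 303 = 728; 195 + 161 + 80 = 436; 388/486 = 79.8%.

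**Retrieval of GP records**
- All: 436/728 = 59.9%
- Intervention: (161 + 80)/425 = 241/425 = 56.7%
- Usual care: 195/303 = 64.4%, so 108 (35.6%) are missing

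**Retrieval by CHAP status, intervention arm**, assuming that the 161 lie within the 176:
- CHAP: 161/176 = 91.5%
- No CHAP, base 425: 80/(425 − 176) = 80/249 = 32.1%
- No CHAP, base 347: 80/(347 − 176) = 80/171 = 46.8%

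**Share of CHAP users**
- Among intervention participants with records: 161/241 = 66.8%
- In the whole arm: 176/425 = 41.4%, or 176/347 = 50.7%

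**How far would booklet returns have to undercount CHAPs done?** For retrieval to be unrelated to CHAP, the number who did it would have to be 161/(241/425) = 284 of 425, or 161/(241/347) = 232 of 347. That is far above 176, and the Discussion says that families often did not attend for the review.

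**Illustration of size.** Assume a usual-care rate of 10% for everyone, a rise to 19% with the CHAP (9 points), and a gain of g points in those without it. With CHAP share s, the difference is 9s + g(1 − s).

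| Gain without CHAP (g) | All 425 (s = 0.414) | The 347 (s = 0.507) | Records only (s = 0.668) | Ratio, base 425 / base 347 |
|---|---|---|---|---|
| 0 | 3.7 | 4.6 | 6.0 | 1.61 / 1.32 |
| 4.5 | 6.4 | 6.8 | 7.5 | 1.18 / 1.11 |
| 9 | 9.0 | 9.0 | 9.0 | 1.00 / 1.00 |

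**Direction.** Let the usual-care rate be a in CHAP users and b in non-users, the CHAP effect be D, and take g = 0 with no selection among controls. The available-case difference minus the true difference is (0.668 − s)(a + D − b). It turns negative only if b exceeds a by more than D.

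**Possible selection in usual care.** If randomisation balanced those who would do the CHAP, about 0.414 × 303 = 125.5 controls are of that kind. They can form at most 125.5/195 = 64.3% of controls with records. Retrieved at 91.5%, they would form 125.5 × 0.915/195 = 58.9%.

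**The case against.** Much of the case on the other side stands, and it limits the point.

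- **Overstatement is not demonstrated.** A reader might infer from the counts that the trial will overstate its effect. The article gives no outcomes by arm or by CHAP status. The 1.3–1.6-fold figures need the diary and classroom teaching to do nothing for those without the CHAP; if those adolescents gain equally, the ratio is 1.
- **Usual care may be filtered too.** A reader might infer that only the intervention arm is selected. But 36% of usual-care records are missing, and GP nomination by carers, GP consent and loss to follow-up apply to both arms. The 41 lost for want of a consenting GP are not split by arm. Enrichment close to that of the intervention arm (up to 64.3% against 66.8%) is compatible with the counts. Equal enrichment would remove imbalance between the arms, but the estimate would still describe a more compliant subset if CHAP users gain more.
- **The 91% is approximate.** The 176 counts booklets returned and the 161 counts people who completed the medical component. The article reports the 176 among the 347, so base 425 is the less certain of the two.
- **The carer survey is a different matter.** A reader might extend the point to carer outcomes. The 79.8% is correct as returned over sent, and the text gives no split by arm or CHAP status. What holds is that 388 is 53.3% of 728.
- **Missing-data methods may be set out in an analysis plan that is not shown.** Their absence here is no error. The definition of the primary set and its label are stated here, as is the evaluable-data restriction.

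**Conclusion.** The concern holds in a limited form. The primary set is available-case under an intention-to-treat label, 40% of participants lack a GP record, and in the intervention arm having one is strongly associated with CHAP uptake. The last statement rests on the 161 lying largely within the 176; the association would survive a sizeable undercount of CHAPs done.

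The GP-record comparison is therefore at risk of bias. Away from the null is the likelier direction, because the CHAP prompts the recording that is counted as outcome. That is a judgement, not a result: it needs CHAP users to gain more than non-users, and non-users not to have a much higher usual-care rate. On the illustration the overstatement lies between none and about 1.6-fold (1.3-fold on the 347 base). Selection among usual-care records is unknown and could change the figure.

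The Discussion's description of response as good needs the 728 base beside it: 60% for GP records and 53% for exit surveys. Even 728 is not everyone randomised, since nine schools withdrew after randomisation and before baseline surveys were sent, with more withdrawals among usual-care than intervention schools.

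**What to change.** 1. Call the primary set available-case, as randomised.
2. Report GP-record retrieval against 728, by arm and, in the intervention arm, by CHAP status. Give exit-survey response as 388/728 alongside 388/486.
3. Compare those with and without records, within each arm, on baseline variables.
4. Specify, before outcomes are compared, a sensitivity analysis by multiple imputation or inverse-probability weighting on baseline variables available in both arms: age, school type, location and baseline-survey response.
5. Add a version that also uses CHAP status in the intervention arm, paired with a tipping-point analysis that varies the assumption about missing usual-care records as well.
6. Draw an intention-to-treat conclusion only if it is robust to steps 4 and 5.

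The CHAP-based version should not become the primary estimate. CHAP status arises after randomisation, exists in one arm only and is reported only for the 347. Returning the intervention arm to 41–51% CHAP users while controls stay enriched, for example at 59%, would itself create imbalance.

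The cost is wording, some programming on data already held, and wider intervals. For CHAP-based weights of 176/161 = 1.09 and 249/80 = 3.11, the Kish inflation is n × Σw²/(Σw)² = 241 × (176²/161 + 249²/80)/425² = 241 × 967.4/180,625 = 1.29. On the 347 base it is 241 × (192.4 + 171²/80)/347² = 241 × 557.9/120,409 = 1.12. Variance in the intervention arm thus rises by a factor of about 1.1–1.3.
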